#### Dose escalation procedure

A schema of the dose escalation procedure and review is shown in figure 2. The sentinel baby is the very first baby recruited to the study and this baby must be greater than 26 weeks GA. The sentinel baby must have received all three administrations of the IMP and have had 72 hours of observed data post administration of third administration before further infants can be recruited for the study. If the first participant does not receive all three doses of the IMP then data will still be collected but they will not qualify as the sentinel baby for this study. All infants recruited after the sentinel baby will be from 23 weeks to 29 weeks and 6 days GA for the remainder of the study. A data and safety monitoring board (DSMB) review of the Neonatal Adverse Event Severity Score (NAESS) data will take place after each infant (for the first three participants at each dose level) has received the final dose of IMP and 72 hours of monitoring. The DSMB will evaluate the safety data before further participants can be recruited, that is, the second or third baby cannot be recruited until data from the first or second baby has been reviewed. This will only be for the first three infants at each dose level, thereafter the data will be reviewed in cohorts of three unless there are safety concerns. Following the recruitment of three infants at any dose level all safety data will be reviewed by the DSMB and they will then advise the Trial Steering Committee (TSC) before a decision is made to (a) move to next dose level or (b) to stay at the same dose level or (c) decrease the dose level or (d) stop the trial. The final decision on dose escalation will be made by the TSC.

**Figure 2 F2:**
[figure not shown]
Schematic overview of the dose escalation design using the continual reassessment method. This schematic overview illustrates the decisional pathway planned. The salmon triangle refers to data review by the data and safety monitoring board (DSMB), which takes place (1) for the first three babies 72 hours after study entry after each baby at each dose level (and confirms no DLE to the management group—termed DSMB assessment), (2) after any potential DLE has been observed (and recommends trial action to trial steering committee (TSC)) and (3) in groups of three babies to make a recommendation to TSC about dose escalation. In the case of 2 or 3, a full data review by the DSMNB is undertaken (identified with a ‘R’). In the event of a suspected DLE, the DSMB will be consulted to recommend to the TSC to continue at the same dose/reduce dose and continue or trial needs to be terminated. If a DLE occurs, then the DSMB may recommend recruitment at the same dose level (eg, ‘grey’ participants) or they may advise dose de-escalation, that is, 2mg/kg down to 1 mg/kg for a further three participants before further review, after which if no DLE occurs they may advise escalation in dose again. In the absence of DLEs, the trial will continue to recruit to the same dose level during DSMB /TSC review periods.

#### Continuous recruitment model during dose escalation decision period

The rationale for continuous recruitment in this trial is to minimise delays to recruitment during the DSMB review for overall dose escalation which takes place after a minimum of three participants at a dose level. It also allows for the trial of the IMP in a larger number of participants at the lower dose levels, allowing for better characterisation of the dose-response curve and the safety profile of rfhSP-D. This means that in the 1 mg/kg and 2 mg/kg cohorts, up to a further two participants can be recruited while the DSMB review dose escalation provided that no DLE has occurred in the first three participants of the dose cohort. The continued recruitment of up to two additional participants at the same or lower dose level while the DSMB conduct their review, will only be permitted if there are no concerns that a DLE has occurred in the cohort under review that is, the first 3 infants under review. Any adverse event (AE) data collected for the additional two recruited participants during DSMB review will then be reviewed by the DSMB once the 72 hours follow-up period is completed. If at any point there are concerns regarding DLEs in these additional participants, but dose escalation has occurred, then this may lead to a de-escalation. The data from the additional participants will be included at that point in the CRM which may recommend dose de-escalation in the middle of the next cohort until further data can be reviewed by the DSMB and the TSC at the next opportunity. This methodology of continual reassessment ensures that infants are only treated at the safest dose level while the safety profile is characterised.

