## Methods and analysis

### Trial design

The study will be conducted in a single-centre, tertiary level 3 neonatal intensive care unit. The study was opened on 6 February 2024 and has a proposed 12-month recruitment period. We aim to recruit 24 infants born between 23 weeks+0 days and 29 weeks+6 days gestation. To date, four infants have been recruited to the study. This study uses a Bayesian continual reassessment model (CRM),^32^,^34^ a model-based design that informs how the dosage of rfhSP-D should be adapted for the next participant cohort based on past trial data. For this first-in-human study, a dose escalation design will be used (figure 1).

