**Figure 1 F1:**
[figure not shown]
Dose escalation process in RESPONSE using rfhSP-D in preterm infants at risk of BPD. *Via Endotracheal tube only. **First iteration will be at 1mg/kg/dose, subsequent iterations 2 mg/kg/dose and 4 mg/Kg/dose. ***Neonatal Adverse Event Severity Score (NAESS). ****administration window of +2 hours. BPD, bronchopulmonary dysplasia; DLE, dose-limiting event; DSMB, data and safety monitoring board; TSC, trial steering committee.

The three dose levels to be considered are 1 mg/kg/dose, 2 mg/kg/dose and 4 mg/kg/dose. Participants will be enrolled at each dose level with a minimum of three participants per dose level. Each participant will receive three doses of rfhSP-D at 0 hours, 12 hours and 24 hours provided that they continue to meet the inclusion criteria and are clinically stable. The first dose of rfhSP-D should be administered after standard surfactant therapy has been given. Whether or not the dose level is escalated will depend on the occurrence of DLEs in all current participants and the doses they have received. A model will be used to estimate the risk of DLE per dose level. Initial estimates of these risks will be updated using data collected throughout the trial. A one-parameter empiric model will be used to describe the relationship between the dose and the probability of observing a DLE. The CRM model will not allow dose-skipping. The target level of DLEs level is set at no greater than 20%. Before the trial, the parameter of the model will be assigned a non-informative prior distribution and initial estimates of DLE probabilities will be derived using model calibration. The recommended phase 2 dose will be defined by considering safety and will be the highest dose level that has an estimated probability of DLE closest but below the target DLE level of no greater than 20%.

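### Escalation can take effect while up to two infants at the current dose are still in their DLE window; the exposure is rare and a simple ordering rule removes it

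*Protocol article*

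**What the plan says.** The general rule is in the protocol article under Trial design (text following the Figure 1 legend): "Whether or not the dose level is escalated will depend on the occurrence of DLEs in all current participants" and on the doses that they received.

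The section on the continuous recruitment model adds that, at 1 and 2 mg/kg, "up to a further two participants can be recruited while the DSMB review dose escalation". This is allowed only if there is no concern about a DLE in the first three. The extra infants' adverse event data go to the DSMB once their 72-hour follow-up is complete. If a concern arises in them "but dose escalation has occurred, then this may lead to a de-escalation". Their data then enter the continual reassessment model (CRM), possibly in the middle of the next cohort. The section closes by saying that the method makes sure that "infants are only treated at the safest dose level while the safety profile is characterised".

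Three safeguards stand elsewhere:
- Dose escalation procedure: the first three infants at each level are taken one at a time, so that "the second or third baby cannot be recruited until data from the first or second baby has been reviewed".
- Figure 2 legend: "In the event of a suspected DLE, the DSMB will be consulted".
- AE reporting: grade 3 or higher events and serious adverse events are reported within 24 hours.

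**The concern.** An infant's DLE window runs for about 96 hours from the first dose: 24 hours of dosing plus 72 hours of observation. An extra infant who enters late in the review can still be inside that window when the decision is taken. The safeguards act once an event is recognised. None of them makes the first infant at the higher level wait for infants still pending below; the one-at-a-time rule starts with the second infant at the new level. An event not yet recognised could therefore become known after a higher dose has been given, and later de-escalation cannot take that dose back.

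At stake is an occasional preterm infant, in a first-in-human study, who receives a dose that the model would no longer recommend a few days later. Two statements in the article are also not true as written: that escalation depends on all current participants, and that the method *ensures* treatment only at the safest level.

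**Working it through.** **1. The plan's own figures.** Calibration with target 0.20, half-width 0.05 and the empiric model, starting from 0.20 at level 3: ln(0.15)/ln(0.25) = 1.3685, so level 2 = 0.20^1.3685 = 0.111 and level 1 = 0.111^1.3685 = 0.049. The stated skeleton of 0.05, 0.11, 0.20 is reproduced. A simulated CRM (normal prior with SD 1.16, cohorts of one, closest-to-target rule, no stopping) gives 2.6/24.9/72.5, 23.0/48.8/28.2 and 0.0/2.8/97.2 for Scenarios 1 to 3. Table 3 has 2.5/24.5/73.0, 22.5/46.5/31.0 and 0.0/3.3/96.7, so agreement is within about 3 points. The prior variance is not stated; 1.34, 2 and 4 are assumed below, with both posterior-mean and plug-in estimates.

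**2. Can a pending infant change the decision?** The rule is closest to 0.20, without skipping.

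| Data | Estimated risks | Result |
|---|---|---|
| 0/3 at 1 mg/kg | all below 0.20 | escalate |
| 1/4 at 1 mg/kg | level 1 0.22-0.28, level 2 0.33-0.38 | stay at level 1, all six settings |
| 1/5 at 1 mg/kg | level 1 0.18-0.23, level 2 0.29-0.33 | stay at level 1, all six settings |
| 1/4 at 2 mg/kg after 0/3 | level 2 0.167-0.198, level 3 0.271-0.292 | stay at level 2, all six settings |
| 1/4 at 2 mg/kg after 0/4 | level 2 0.152-0.180, level 3 0.253-0.272 | stay at level 2, all six settings |
| 1/4 at 2 mg/kg after 0/5 | | depends on the estimator |
| 1/5 at 2 mg/kg after 0/3 or 0/4 | | depends on the estimator |
| 1/5 at 2 mg/kg after 0/5 | | escalate, all six settings |

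With a tighter prior (SD 0.75), 1/5 at 1 mg/kg also depends on the estimator: plug-in risks of 0.146 and 0.242 favour level 2, while the posterior mean stays at level 1.

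**3. How often would it happen?** Let λ be the accrual per day, W = 4 days the window, and p the DLE risk at the current level. Take the worst timing, with the event recognised only at hour 96, and a review of at least 4 days. A pending infant has remaining time u between 0 and 4 days, and the next infant arrives within u with probability 1 − exp(−λu). Integrating over u:

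expected exposures ≈ p × [λW − (1 − exp(−λW))].

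This ignores the cap of two and counts every DLE as a reversal, so it is slightly high.
- Planned accrual: λ = 24/365 = 0.0658 per day and λW = 0.263. The bracket is 0.263 − 0.231 = 0.032.
- First escalation, p = 0.02, 0.05 and 0.10 (Scenarios 3, 1, 2): about 0.06%, 0.16% and 0.32%.
- Second escalation, p = 0.20 (Scenario 2): about 0.6%.
- Accrual so far: "To date, four infants have been recruited to the study". Taking the date of protocol V.4.0 as the earliest date of that count, 6 February to 24 July 2024 is 169 days, and 4 × 366/169 = 8.7 per year or less. Then λW = 0.095 and the bracket is 0.0953 − 0.0909 = 0.0044, giving about 0.04% at p = 0.10 and 0.09% at p = 0.20.

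Simulation with the cap and review times of 2 to 28 days agrees. At 24 per year the first escalation gives 0.03-0.07%, 0.08-0.16% and 0.14-0.32% in Scenarios 3, 1 and 2. It gives about 0.01-0.1% if recognition is uniform over the window. The second escalation gives about 0.02-0.6%.

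**4. Effect on the recommended dose.** Even if both extra infants were always pending and one infant was always dosed at the next level before they read out, Scenario 2 recommendations are 21.9/48.2/29.9 as written and 20.9/49.8/29.3 with a hold. The largest difference is 1.6 points.

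**The case against.** The strongest reply is that this is an openly stated trade-off. The section gives its reasons, caps the extra infants at two, limits them to the two lower doses, requires a clean first three, and provides for late DLEs. The all-current-participants sentence can be read as the general principle and the recruitment section as its specific exception. A hold might also be written into the full protocol or the DSMB charter, which are not shown.

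Much of this stands. The choice is disclosed and mostly protected. But the text does not call the recruitment section an exception, and even on that reading the closing assurance conflicts with the provision, in the same section, for de-escalating after escalation.

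Three stronger readings are tempting, and the document does not support them:
- A reader might infer that the decision uses the first three infants only. That phrase sits in the condition for continued recruitment; the Dose escalation procedure has all safety data reviewed.
- A reader might infer that nothing on the extra infants is seen before their 72 hours end. Concerns can be raised at any point, a potential DLE triggers a full DSMB review, and serious events are reported within 24 hours. Only unrecognised events are affected.
- A reader might take the risk as (1−p)³ × [1 − (1−p)²], which is 3.7% to 18.4% for p from 0.02 to 0.20. That assumes both extra infants are always pending and a higher-dose infant always arrives first. At planned accrual an infant is pending at only 12-23% of escalations.

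**Conclusion.** The point holds as a small gap in ordering and wording. Escalation may take effect before infants already dosed at the current level have completed their DLE window, and no stated rule prevents a higher dose in the meantime. The exposure is at most about 0.6% per escalation at 24 infants per year and about 0.1% at the accrual seen so far. One-at-a-time entry limits it to about one infant. The 2 mg/kg dose is at or below the 20% target in all three of the plan's scenarios; 4 mg/kg exceeds it only in Scenario 2, at 0.30.

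The mismatch in the text is certain. The size rests on assumptions: review time, prior variance, estimator and time of recognition are not given. Reversal at the second escalation is sensitive to the estimator. The 96-hour window follows the Dose escalation procedure. This is an optional improvement, not a flaw that threatens the trial or its recommended dose.

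**What to change.** State under Trial design and in the continuous recruitment section that the first infant at a higher level is not dosed until three things are done:
- every infant already dosed has completed the 72-hour follow-up;
- the DSMB has confirmed their DLE status;
- the CRM has been re-run with those outcomes.

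Meanwhile, keep recruiting at the current level within the cap of two. Replace the assurance built on *ensures* with wording such as: *is intended to limit exposure above the recommended dose level*.

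The cost is small. With λ as above and a review of at least 4 days, the mean wait from infants pending at the decision is 4 − 0.2313/0.06575 = 0.48 day; across review times of 2 to 28 days the mean is about 0.3-0.5 day per escalation. The wait is at most about 4 days after the last extra infant, or about 8 days in total if a second enters during the wait. The DSMB check comes on top: with an assumed 1 to 3 days, the mean total is 0.4-1.6 days. About 0.01-0.05 infants per escalation would be missed because the cap is reached. Continuous recruitment keeps its purpose.

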### Study intervention and outcomes

#### Eligibility criteria

All preterm infants born before 30 weeks of gestation, intubated and treated with surfactant for RDS who are considered clinically stable are eligible. Eligibility will be confirmed within 2 hours of admission to the neonatal unit and reconfirmed for each participant before the IMP is administered.

#### Inclusion criteria

Inborn infants born between 23 weeks and 0 days and 29 weeks and 6 days of gestation (<30 weeks), who are:Intubated or intubation planned for RDS at the time of eligibility check within 12 hours from the time of birth.Receiving standard surfactant replacement therapy.Clinically stable on mechanical ventilation—clinical stability is defined at the time of IMP instillation and is defined below.Written informed consent from parents/guardians/person with legal responsibility has been given.

#### Definition of clinical stability

Eligibility of the participant must be rechecked prior to administration of the IMP given the varying clinical status of these infants. Stability will consider if the following are true:

Blood gas parameters within the normal range for preterm infants (pH>7.20; paCO_2_<8 kPa).Mean blood pressure with or without inotropic support at a value in mm Hg at least numerically equivalent GA in weeks or above.No evidence of a pneumothorax.Clinical observations within acceptable range for an infant of that GA.The attending neonatologist considers the infant to be clinically stable.

#### Exclusion criteria

Congenital anomalies (ie, any major antenatal diagnosed congenital abnormality) such as congenital heart disease, suspected or known chromosomal abnormalities.Infants requiring only non-invasive respiratory support, that is, no endotracheal intubation.Infants born in very poor condition and judged too sick or unstable to be included (high risk of imminent mortality) in an experimental first-in-human study; for example, infants that require maximal intensive care therapy and have findings such as a grade IV intraventricular haemorrhage that may be life-limiting.Infants that are born outside the participating site.Participation in any other interventional study (participation in another observational study is permissible).Parents/legal guardians are unable to give consent due to learning or other difficulties.

### Recruitment and informed consent

The study team will monitor admissions of any women in threatened or established preterm labour. Any identified women will be approached by the study team to discuss and consider the study and verbal consent for participation will be taken. All parents/legal guardians of eligible participants will be approached if the baby is born and remains eligible for informed written consent. If the person(s) providing consent on behalf of the infant does not speak English, every effort will be made to use translational service to provide an opportunity to participate in the study. If the investigator is not able to confidently take informed consent the infant will not be recruited to the study.

### Study intervention

The recombinant fragment of SP D drug product has been manufactured to good manufacturing practice and is known as rfhSP-D in this study. The IMP has orphan designation with the Food and Drug Administration. The sterile IMP is formulated in 0.9% saline at a concentration of 1 mg/mL in 2 mL vials. The first administration of rfhSP-D will be given as soon as possible after administration of standard-of-care surfactant therapy, this will be known as T0. Subsequent administration will be given at T0+12 (±2) hours and T0+24 (±2) hours. If the infant requires further standard surfactant therapy which coincides with the time of IMP administration, then the IMP should be given after the standard surfactant therapy has been administered. The IMP will be administered via a surfactant giving set that is inserted into the endotracheal tube. If the participant is extubated before any IMP dose is scheduled, then the IMP will not be administered. Vital signs will be monitored every 15 min for the first hour after administration of the IMP. The study drug can be administered by any authorised medically trained delegate. Eligibility criteria will be confirmed prior to each administration.

#### Criteria for discontinuing participation in the trial

Any dose modifications in this protocol will be in line with the trial design and according to the dose level confirmed by the DSMB and the TSC.

Reasons that the intervention may be discontinued are as follows:

Any change in the infant’s condition that in the clinician’s opinion justifies the discontinuation of treatment.Withdrawal of consent for treatment by the parent/guardian/legal representative.

Participants who discontinue protocol treatment, for any of the above reasons, will remain in the trial for follow-up and data analysis. The study team does not anticipate problems with intervention adherence given that RESPONSE is an inpatient-based study. All participants in the study will receive standard neonatal care and there will be no alteration in their clinical management. The study does not require any additional follow-up of the participants recruited once they are discharged from the hospital or reach 40 weeks PMA. The hospital where the participant is being cared for is responsible for any medical care. The sponsor holds indemnity for any trial-related harm caused to the participant.

### Study outcomes

The primary outcome of this study is to assess the safety profile of rfhSP-D across three dose levels and to identify the RP2D. DLEs will be identified using clinical criteria and grading as described below.

### Dose-limiting events

The severity of all AE and/or adverse reactions (serious and non-serious) in this trial will be graded using the toxicity graded in the NAESS V.1.0.^35^ The NAESS has been developed as existing scores such as the Common Terminology Criteria for Adverse Events is not suitable for use in a study involving neonates. The NAESS developed by the International Neonatal Consortium has been developed to facilitate the conduct and appropriate interpretation of neonatal clinical trials such as RESPONSE.^36^

Grades for neonatal-specific AEs according to the NAESS V.1.0^35^ are:

Grade 1: Mild; asymptomatic or mild symptoms; clinical or diagnostic observations only; no change in baseline age-appropriate behaviours^*^; no change in baseline care or monitoring indicated.

Grade 2: Moderate; resulting in minor changes of baseline age-appropriate behaviour^*^; requiring minor changes in baseline care or monitoring^*+^.

Grade 3: Severe; resulting in major changes of baseline age-appropriate behaviour^*^ or non-life-threatening changes in basal physiological processes^+^ requiring major change in baseline care or monitoring^**_._^

Grade 4: Life-threatening; resulting in life-threatening changes in basal physiological processes^+^; requiring urgent major change in baseline care***.

Grade 5: Death.

*Age-appropriate behaviour refers to oral feeding, voluntary movements and activity, crying pattern, social interactions and perception of pain.

^+^Basal physiological processes refer to oxygenation, ventilation, tissue perfusion, metabolic stability and organ functioning.

**Minor care changes constitute: brief, local, non-invasive or symptomatic treatments.

*** Major care change constitute: surgery, the addition of long-term treatment and upscaling care level.

The DSMB will determine the occurrence of a DLE based on the following criteria:

A single event defined as grade 3 or above on the NAESS that is possibly, probably or definitely thought to be related to the IMP. Relatedness will be confirmed by an independent neonatologist at the participating site.A single serious AE (SAE) that is possibly, probably or definitely thought to be related to the IMP. Relatedness will be confirmed by an independent neonatologist at the participating site.Concerns over frequency of any AEs reported at grade 2 on the NAESS that are possibly, probably or definitely thought to be related to the IMP.

Secondary outcomes related to efficacy for this study are as follows:

Evaluation of systemic absorption of rfhSP-D using serial measurements of SP-D in plasma and its continued presence in tracheal fluid.To determine the effect of rfhSP-D on inflammatory markers in the lung secretions (eg, cell counts of neutrophils, macrophages, lymphocytes, IL-8, IL-6, IL-1).To compare the clinical effects of endotracheal administration of rfhSP-D on physiological and intensive care parameters in treated infants in this trial with non-treated infants from a parallel observational study.

